# Efficacy and Safety of Pharmacokinetically-Driven Dosing of Mycophenolate Mofetil for the Treatment of Pediatric Proliferative Lupus Nephritis–A Double-Blind Placebo Controlled Clinical Trial (The Pediatric Lupus Nephritis Mycophenolate Mofetil Study)

**Published:** 2024-05-13

**Keywords:** Pediatric, Lupus, Childhood-onset, SLE, Lupus nephritis, Mycophenolate mofetil, Pharmacokinetics

## Abstract

**Background::**

The safety and efficacy of mycophenolate mofetil (MMF) for lupus nephritis (LN) treatment is established in adults and in some children. MMF is rapidly converted to the biologically active metabolite mycophenolic acid (MPA) whose pharmacokinetics (PK) is characterized by large inter- and intra-individual variability.

**Methods/Design::**

This randomized, double-blind, active comparator, controlled clinical trial of pediatric subjects with proliferative LN compares pharmacokinetically-guided precision-dosing of MMF (MMF_PK_, i.e. the dose is adjusted to the target area under the concentration-time curve (AUC_0–12h_) of MPA ≥ 60–70 mg*h/L) and MMF dosed per body surface area (MMF_BSA_, i.e. MMF dosed 600 mg/m^2^ body surface area), with MMF dosage taken about 12 hours apart. At baseline, subjects are randomized 1:1 to receive blinded treatment with MMF_PK_ or MMF_BSA_ for up to 53 weeks. The primary outcome is partial clinical remission of LN (partial renal response, PRR) at week 26, and the major secondary outcome is complete renal response (CRR) at week 26. Subjects in the MMF_BSA_ arm with PRR at week 26 will receive MMF_PK_ from week 26 onwards, while subjects with CRR will continue MMF_BSA_ or MMF_PK_ treatment until week 53. Subjects who achieve PRR at week 26 are discontinued from study intervention.

**Discussion::**

The Pediatric Lupus Nephritis Mycophenolate Mofetil (PLUMM) study will provide a thorough evaluation of the PK of MMF in pediatric LN patients, yielding a head-to-head comparison of MMF_BSA_ and MMF_PK_ for both safety and efficacy. This study has the potential to change current treatment recommendations for pediatric LN, thereby significantly impacting childhood-onset SLE (cSLE) disease prognosis and current clinical practice.

## INTRODUCTION

Systemic lupus erythematosus (SLE) is a multi-organ autoimmune disease with relatively increasing mortality that often targets young women and children of U.S. minorities [1–3]. Childhood-onset SLE (cSLE) has similar manifestations as lupus in adults, but childhood-onset disease is accompanied by more severe multi-organ involvement, including LN in up to 80% of affected children [4–6].

Although the use of cyclophosphamide (CYC) has long been regarded the standard of care in proliferative LN [7], MMF is similarly accepted as a cornerstone of LN therapy [8], with a more favorable side-effect profile compared with CYC [9]. Off-label use for the treatment of LN in Europe and the U.S. is supported by recommendations of the American College of Rheumatology (ACR) [10] and the European League against Rheumatism (EULAR) [11]. The safety and efficacy of MMF in LN have been tested in adults and in some pediatric subjects. However, since the optimal MMF dosing to achieve improvement in LN in cSLE is not well-established [12], the pediatric renal transplant dosing regimen of MMF based on weight or body surface area (BSA) has been adopted instead.

MMF, an ester prodrug, is rapidly converted to the biologically active moiety mycophenolic acid (MPA, Figure 1). Exposure to MPA is associated with MMF’s immunosuppressive and anti-inflammatory effect and the patient’s clinical response. However, the PK of MPA is characterized by large inter-individual and intra-individual variability. Factors contributing to this variability include differences in albumin concentration, corticosteroid use, impaired renal function, altered hepatic function, and genetic polymorphisms in drug metabolizing enzymes and drug transporters. Our previous work and that of other researchers [12–15], have shown that there is only a weak correlation between the dose of MMF (either based on weight or BSA) and the area under the time-concentration curve of MPA (MPA-AUC_0–12_). The apparent disconnect between MMF dosing based on body weight or BSA and MPA exposure stems from MPA’s complex metabolism which is influenced by concurrent therapies, the subject’s pharmacogenetic make-up, and presence of systemic disease including liver and renal function, which have all been extensively investigated by our group [12,16–20]. However, it remains uncertain whether higher MPA exposure with MMF dosing based on PK is well-tolerated, safe, and produces better renal outcomes compared to MMF dosing based on BSA when used for the treatment of pediatric LN. This underscores the need for therapeutic drug monitoring to optimize the use of MMF in pediatric LN. In this current study, our group aims to yield high-quality evidence for the superiority of pharmacokinetically-guided precision dosing over BSA-based dosing of MMF in pediatric LN.

## METHODOLOGY

### Design

This is a randomized double-blind active comparator clinical trial of pediatric subjects (8 to<18 years of age) with proliferative LN as per the International Society of Nephrology/ Renal Pathology Society (ISN/PRS) classification criteria [21]. All eligible subjects are randomized at baseline to one of 2 arms: the current standard of clinical care (MMF_BSA_) or pharmacokinetically-guided precision dosing (MMF_PK_). Subjects in the MMF_BSA_ arm who achieve PRR at week 26 will be switched to the MMF_PK_ arm. At the end of Part 1, subjects in the MMF_PK_ arm with CRR or PRR or MMF_BSA_ arm subjects with CRR will continue their respective treatment arms during Part 2 of the study. At week 26 (end of Part 1) treatment non-responders, i.e. subjects who did not achieve PRR at week 26, will be discontinued from active medication management in the study but will still be monitored for a total of 53 weeks. The MMF starting dose for both treatment arms will be the recommended MMF dose for pediatric LN at 600 mg/m^2^ twice daily, about 12 hours apart [22]. Only in the MMF_PK_ arm will the MMF dose be adjusted for a target MPA-AUC_0–12_ of 60 mg*h/L, with initial Bayesian PK-profiling performed after drug steady state is achieved. A schema of the study design is shown in Figure 2.

The study is overseen by a Centralized Coordinating Center (CCC), a study steering committee which includes a representative of the Lupus Foundation of America, and an independent Data Safety Committee that was selected by the National Institute of Arthritis and Musculoskeletal and Skin Diseases (NIAMS).

### Setting

The study will be conducted at 19 U.S. sites, all located at major pediatric academic centers. Site investigators are listed in ClinicalTrials.gov (NCT05538208). Site investigators are either board-certified pediatric rheumatologists or pediatric nephrologists.

### Population

Study participation is not restricted by patient sex, race, or ethnicity. Eligible patients fulfill all inclusion and no exclusion criteria. Given the potential use of immunosuppressants other than MMF for the treatment of proliferative LN, the decision to choose MMF is made as part of clinical care. The complete listing of the key eligibility criteria is provided in Table 1, while Supplementary Table 1 provides a full listing. Information about prohibited concurrent medications is shown in Supplementary Table 2.

### Outcome measures and safety and efficacy endpoints

The primary efficacy outcome of the study is the improvement of proliferative LN as measured by the presence of at least PRR at the end of Part 1 of the study (week 26). The major secondary outcome is the achievement of CRR at the end of Part 1 of the study. Other secondary outcomes are the achievement of CRR at the end of Part 2 of the study (week 53) and frequency of adverse events defined as grade 3 or higher during all parts of the study using the National Cancer Institute Common Terminology Criteria for Adverse Events.

Exploratory outcomes include: change in Renal Activity Index for Lupus (RAIL) score (baseline visit to week 53) [23,24], rate of LN flares, time to PRR and CRR during the study (baseline visit to week 53), mean time-adjusted score of the Systemic Lupus Erythematosus Disease Activity Index (SLEDAI) [25], considering extra-renal domain items during the study (baseline visit to week 53), cumulative dose of oral corticosteroids (CS; in prednisone-equivalents) and cumulative exposure to intravenous CS during the study, frequency of patients fulfilling discontinuation criteria during the study, change in health-related quality of life as measured by the Pediatric Quality of Life Inventory (PedsQL) Generic Core Scale [26], during the study, percentage of patients with intake of ≥ 80% of prescribed MMF doses as per blister-pack count during the study, and presence of MPA-levels<0.1 mg/L from random testing or in-clinic testing during the study. The MPA primary and secondary outcome evaluations will be performed by independent blinded evaluators at the CCC, according to validated criteria. Outcome definitions are provided in Table 2.

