### Sample size and power estimation

The PLUMM study is the largest clinical trial in pediatric LN, to the best of our knowledge, which is adequately powered. Sample size was determined from a combination of prevalence data and precedents in the literature [13,14,35–43]. A sample size of 45 subjects per group with proliferative LN is anticipated to provide a power of 80% for the primary aim of detecting a significant difference in the rate of PRR between the MMF_PK_ and MMF_BSA_ arms at the end of Part 1, at a 2-sided 5% significance level by a two-group Chi-square test, assuming the rate of PRR is 55% in MMF_BSA_ and 83% in MMF_PK_. The sample size of 90 will ensure 81% of power to detect a statistically significantly difference in the rate of CRR between the two study arms, assuming a smaller proportion of 14% and a larger proportion of 43%. Based on the above presented power analyses, we will plan to enroll 105 subjects, to allow for up to 14.3% attrition rate during Part 1 of the study.

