### Statistical analysis

The primary outcome, superiority of MMF_PK_ over MMF_BSA_ for the percentage of subjects with clinical remission of LN (PRR, CRR) at the end of Part 1, will be tested using the analytical approach for the binomial outcome, such as Chi-square test, Fisher’s exact test, or a Bayesian approach with non-informative Beta prior for the binary probability parameter.

The choice of approach will be determined by the distribution of the data. Subjects who discontinue the treatment due to any reason will be considered as being non-responders. All secondary and exploratory efficacy outcomes will be analyzed by treatment group. For the binary secondary or exploratory outcomes, the analytical approach for the binary outcome, as used for the primary analysis, will be performed.

For the continuous exploratory endpoints, including change from baseline in PROMIS scores or RAIL scores, a mixed-effect model with repeated measures will be applied. The Kaplan-Meier plots will be generated for the exploratory endpoints of time to CRR and time to PRR. Since no measures are collected from the discontinued subject, the analyses will take an Inverse Propensity Weighting (IPW) approach where the propensity for subjects to be discontinued from each arm are estimated using logistic regression modeling or the covariate balance propensity score method.

The IPW approach will create pseudo subject samples that represent the original randomized subject cohort at the beginning of the study, and therefore addresses the missing data issue due to subject discontinuation.

Descriptive/summary statistics for all endpoints, with 95% confidence interval for treatment difference, will be provided. Baseline demographic characteristics, primary and major secondary outcomes will also be summarized overall and by age (<12 years ***vs.*** ≥12 years), gender and race (white ***vs.*** non-white). Safety analysis will be performed on all subjects who received at least one dose of study drug. Safety data will be subject to clinical review and summarized by appropriate descriptive statistics.

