Notably, the SSR has been specifically developed for the PLUMM study in an international effort that used state-of-the art consensus methodology, statistical modeling, and true disease courses of children with LN. In brief, the SSR considers the time since LN diagnosis, the course of LN and extrarenal SLE, as well as the prior CS dosage since the preceding clinical assessment of the subject to suggest the dose of oral prednisone or IV methylprednisolone. Standardization of CS use is important, as CS are potent effect modifiers that require careful dosing in any randomized clinical trial of an inflammatory disease and has been identified to be one of the significant factors impacting the success of clinical trials in lupus [45,46]. This SSR is anticipated to manage and reduce variability of CS dosage using international consensus and real-life cSLE patient data.

The study design has some limitations. The feasibility of recruitment may be affected by the need in some patients for therapy with IV cyclophosphamide and/or B-cell depletion therapy (rituximab or belimumab). If such is deemed necessary for the treatment of a patient leading to their discontinuation of the study, their clinical outcome will still be monitored longitudinally. Concurrent use of calcineurin inhibitors may also affect MPA PK, so a subanalysis may be performed in those patients receiving this. Given the complex clinical course of cSLE patients, variability in CS dosing may persist despite SSR use, leading to potential deviation from the proposed standardized steroid regimen. If this was to be the case, then we will correct analyses for variation in CS dose and consider Bayesian analysis with causal interference strategies to correct for the CS effect. Since high doses of CS decrease exposure to MPA, we will repeat MPA PK measurement if a patient’s CS dose has changed by>50% or>20 mg since the last MPA PK profile. MPA PK may also be affected by concurrent medications. However, these will be kept stable during the study, other than CS.

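### The article contradicts itself on follow-up after discontinuation, so the observation window for grade 3+ adverse events is unsettled and could depend on response

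*Protocol article*

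**What the plan says.** The outcomes section names as a secondary outcome the "frequency of adverse events defined as grade 3 or higher during all parts of the study". It therefore spans Part 1 (to week 26) and Part 2 (to week 53).

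Three statements bear on what is recorded once a subject stops study treatment:

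- Design: week-26 non-responders "will be discontinued from active medication management in the study but will still be monitored for a total of 53 weeks".
- Discussion, on subjects who leave because they need other therapy: "their clinical outcome will still be monitored longitudinally".
- Statistical analysis, in the text on the continuous and time-to-event exploratory endpoints: "Since no measures are collected from the discontinued subject, the analyses will take an Inverse Propensity Weighting (IPW) approach".

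On safety itself, the Statistical analysis section says "Safety analysis will be performed on all subjects who received at least one dose of study drug" and calls for descriptive summaries. It also says, of every endpoint, "Descriptive/summary statistics for all endpoints, with 95% confidence interval for treatment difference, will be provided". The Design section moves MMF_BSA subjects with PRR to MMF_PK at week 26.

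**The concern.** Monitoring to week 53 and collecting no measures after discontinuation cannot both be true of the same subjects. Neither statement says whether adverse events are recorded after discontinuation, yet the secondary safety outcome runs across that point.

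The group affected is defined by response, and the plan expects response to differ between the arms. If the no-measures statement is applied to adverse events, harm is watched for 26 weeks in non-responders and 53 weeks in responders. The arm with more responders is then watched for longer. The Introduction makes it an open question whether higher MPA exposure is tolerable and safe, so the length of observation in each arm matters. Events that were never collected cannot be recovered by a later analysis rule.

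**Working it through.** **Inputs from the article**

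- Response at week 26 (Sample size section): "assuming the rate of PRR is 55% in MMF_BSA_ and 83% in MMF_PK". I read this as at least PRR, which is the primary outcome. Non-responders are then 45% (MMF_BSA) and 17% (MMF_PK).
- Part 1 ends at week 26 and the study at week 53, so Part 2 lasts 27 weeks.
- CRR at week 26 is assumed to be 14% and 43% (same section). I take 14% to be MMF_BSA, so 55 − 14 = 41 percentage points of that arm have PRR only and switch.
- The article gives no adverse-event rate, person-time or safety power, so there is no stated safety figure to reproduce.

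**My assumptions:** no other dropout; constant event rate unless stated; the Design section's account of who is discontinued. The Abstract instead has subjects achieving PRR discontinued from study intervention. That also needs reconciling, because it changes who would fall under the no-measures statement.

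**Step 1. Mean observation time** = 26 + 27 × [p + (1 − p) × m], where p is the response rate, m = 0 if non-responders are unobserved after week 26, and m = 1 if they are monitored to week 53.

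| Reading | MMF_BSA | MMF_PK | Count ratio at equal event rates |
|---|---|---|---|
| No measures (m = 0) | 26 + 27 × 0.55 = 40.85 weeks | 26 + 27 × 0.83 = 48.41 weeks | 48.41 / 40.85 = 1.185 |
| Monitored (m = 1) | 53 weeks | 53 weeks | 1.00 |

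**Step 2. Events concentrated early (m = 0).** If 60% of 53-week events fall in Part 1, the observed shares are 1 − 0.45 × 0.40 = 0.820 and 1 − 0.17 × 0.40 = 0.932, ratio 1.137. If 70% do, they are 0.865 and 0.949, ratio 1.097.

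**Step 3. Proportion with at least one event (m = 0).** Assume a true 53-week proportion of 40% in both arms. Then H = −ln(0.60) = 0.511, and the 26-week proportion is 1 − exp(−0.511 × 26/53) = 0.222.

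- MMF_BSA: 0.45 × 0.222 + 0.55 × 0.40 = 0.320
- MMF_PK: 0.17 × 0.222 + 0.83 × 0.40 = 0.370

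The artefact is 5 percentage points. Over assumed annual event rates of 0.1 to 1.2 per subject it runs from 1.35 points (7.5% against 8.9%) to 7.1 points (59.1% against 66.2%).

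**Step 4. The week-26 switch.** Set the event rate to 1 on MMF_BSA, r on MMF_PK, and q in non-responders after week 26.

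- Unobserved non-responders: MMF_BSA events are 26 + 27 × (0.14 + 0.41r) = 29.78 + 11.07r; MMF_PK events are 48.41r. The crude ratio exceeds r only while 29.78 + 11.07r < 48.41, that is, r < 1.68. At r = 2 it is 96.82 / 51.92 = 1.86, below the true 2. Per person-time it is 2.00 / (51.92 / 40.85) = 1.57.
- Monitored non-responders add 27 × 0.45q = 12.15q and 27 × 0.17q = 4.59q. With r = 1.5 and q = 1 the ratio is 77.21 / 58.54 = 1.32. With r = 1 and q = 1.5 it is 55.30 / 59.08 = 0.94.

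The as-randomised 53-week ratio can therefore lie above or below the true one.

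**The case against.** The strongest reply is that the design is clear where it matters. The Design section speaks directly about week-26 non-responders and keeps them monitored, and the Discussion points the same way for subjects who leave for other therapy. The no-measures clause sits with the exploratory endpoints and explains why weighting is used there; safety has its own sentences. On that reading, planned observation is equal and nothing needs correcting. This stands as one of two possible readings. It does not settle the matter: the Discussion speaks of clinical outcome only, neither source mentions adverse events, and the clause is written without restriction to particular endpoints.

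A second reply is that a crude comparison is not stated. That also stands. The word frequency, the dosed-subject population and descriptive summaries do not fix a denominator, and an analysis plan that is not shown may specify person-time. The crude ratio is what an unadjusted count would show, not what the article commits to. The contradiction over collection remains whichever denominator is used.

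A reader might go further and infer that MMF_PK will look more harmful than it is. The documents do not support that. It needs the no-measures clause to govern adverse events, and even then the switch dilutes a true difference, so that above a true rate ratio of about 1.68 the excess is understated.

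Finally, the size is modest against the trial's precision. With about 50 subjects per arm and proportions near 35%, the 95% interval for a difference is roughly ±1.96 × √(2 × 0.35 × 0.65 / 50), or ±19 points. That limits the consequence, but a systematic difference in observation time should not be left in when wording can remove it.

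**Conclusion.** The point holds as a contradiction with a conditional consequence. The article both monitors week-26 non-responders to week 53 and says discontinued subjects yield no measures, and it leaves open which applies to grade 3+ adverse events.

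If the no-measures statement applies, observation depends on response: 40.9 against 48.4 weeks, with a crude count ratio of about 1.19 at equal constant event rates (1.10 to 1.14 if 60% to 70% of events fall in Part 1). This rests on the plan's 55% and 83% response rates, no other dropout, and the Design section's account of who is discontinued. If the monitoring statement applies, the artefact is nil. On either reading, the week-26 switch leaves the net direction of the whole-study comparison uncertain. This is worth correcting while adverse events can still be collected prospectively.

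**What to change.** 1. Reconcile the Statistical analysis section with the Design section. State that grade 3+ adverse events in discontinued subjects are recorded to week 53, on the monitoring the Design section already describes, and are included in the safety analysis. Align the Abstract's sentence on who is discontinued.
2. Make weeks 0-26 the main between-arm harm comparison. That window closes before the response-dependent discontinuation and the switch, and its planned length is the same in both arms.
3. Report Part 2 and whole-study events with person-time denominators, as supportive results.

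The cost is wording, with no extra subjects or procedures, provided the monitoring in the Design section is in fact carried out; if it is not, recording events to week 53 is added work. There are two downsides. The main harm comparison will contain fewer events. Person-time rates do not remove bias if follow-up ends because of non-response, nor do they undo the dilution from the switch, which is why they are supportive only.

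### The protocol contradicts itself on data after discontinuation, and the unscaled cumulative steroid dose compares the arms fairly only if week-26 non-responders' steroid use is recorded to week 53

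*Protocol article*

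**What the plan says.** In the Protocol article, the section on outcome measures lists as exploratory the "cumulative dose of oral corticosteroids (CS; in prednisone-equivalents) and cumulative exposure to intravenous CS during the study". In the same list, the extra-renal SLEDAI score is a time-adjusted mean, whereas the steroid outcome is a raw total.

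Three places bear on how long that total accumulates:

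- **Design**, on subjects without partial renal response (PRR) at week 26: they "will be discontinued from active medication management in the study but will still be monitored for a total of 53 weeks".
- **Discussion**, on subjects who leave because they need other therapy: "their clinical outcome will still be monitored longitudinally".
- **Statistical analysis**: "Since no measures are collected from the discontinued subject, the analyses will take an Inverse Propensity Weighting (IPW) approach". The weighting is said to represent the original randomised cohort, so that it "addresses the missing data issue due to subject discontinuation".

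The Design section also switches MMF_BSA subjects with PRR to MMF_PK dosing at week 26. The sample size rests on different response rates in the two arms: "assuming the rate of PRR is 55% in MMF_BSA_ and 83% in MMF_PK".

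**The concern.** A raw sum is comparable between arms only when observation time is comparable. Here the rule that ends study medication management is failure to respond at week 26, and the trial is planned on the expectation that this happens far more often in one arm: 45% of MMF_BSA against 17% of MMF_PK. If steroid recording ends with discontinuation, the arm with more failures loses more of its weeks 27 to 53, and its total is pulled down for that reason alone. A real steroid-sparing effect of MMF_PK could be shrunk, hidden or reversed. This matters because the article treats steroids as a strong influence on outcome and builds a standardised regimen to control them, so readers will look at this comparison.

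**Working it through.** The document gives no figure for the steroid outcome, so there is none to reproduce.

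**Inputs from the document.** Response rates are 55% and 83% (Sample size and power estimation). Part 1 ends at week 26 and the study at week 53 (Design). The check follows the Design section's rule that subjects without PRR stop at week 26. One sentence of the Abstract instead discontinues those who achieve PRR, and that must be reconciled too. Dropout before week 26 is ignored.

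**Mean accumulation time.** With T the last week recorded for non-responders, mean weeks = response rate × 53 + (1 − response rate) × T.

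- T = 53 (Design): 53 weeks in both arms, so no truncation.
- T = 26 (Statistical analysis):
  - MMF_BSA: 0.55 × 53 + 0.45 × 26 = 29.15 + 11.70 = 40.85 weeks.
  - MMF_PK: 0.83 × 53 + 0.17 × 26 = 43.99 + 4.42 = 48.41 weeks.
  - Difference 7.56 weeks; ratio 48.41 / 40.85 = 1.185.

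**Effect on the total.** Doses are not given, so two factors are assumed. Let f be the Part 2 daily dose as a fraction of the Part 1 dose, and a the non-responder daily dose relative to the responder dose. Setting the responder Part 1 dose to 1 per week, a responder's total is 26 + 27f. A non-responder's total is 26a if truncated, or a(26 + 27f) if complete.

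| f | a | MMF_PK vs MMF_BSA, all followed to week 53 | MMF_PK vs MMF_BSA, non-responders stop at week 26 |
|---|---|---|---|
| 1 | 1 | 0% | +18.5% |
| 0.5 | 1 | 0% | +11.3% |
| 0.25 | 1 | 0% | +6.4% |
| 1 | 1.25 | −6.3% | +13.1% |
| 0.5 | 1.25 | −6.3% | +5.4% |
| 0.25 | 1.25 | −6.3% | +0.2% |
| 0.25 | 1.5 | −11.4% | −4.9% |

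Example, last row: the responder total is 26 + 27 × 0.25 = 32.75 and the truncated non-responder total is 26 × 1.5 = 39. MMF_BSA is 0.55 × 32.75 + 0.45 × 39 = 35.56; MMF_PK is 0.83 × 32.75 + 0.17 × 39 = 33.81; the ratio is 0.951. With complete data it is (0.83 + 0.17 × 1.5) / (0.55 + 0.45 × 1.5) = 1.085 / 1.225 = 0.886.

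In every row truncation moves the comparison against MMF_PK. The sign of the result is not fixed: MMF_BSA shows the lower total only when 26a < 26 + 27f.

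**Can the weighting repair it?** Weighting lets subjects who remain stand in for similar subjects who left. After week 26 no non-responder remains. If week-26 response enters the propensity model, a non-responder's probability of staying is zero and no weight exists. If it is left out, responders stand in for non-responders.

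**With complete follow-up.** Assume that the 55% includes complete responders and that the 14% complete-response rate is the MMF_BSA figure. The MMF_BSA arm then divides after week 26 into 14% still on BSA dosing, 55 − 14 = 41% switched to MMF_PK, and 45% off study medication management.

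**Would dividing by time observed help?** With truncation and a = 1, a responder's mean rate at f = 0.25 is 32.75 / 53 = 0.618 and a non-responder's is 1. MMF_BSA is 0.55 × 0.618 + 0.45 = 0.790; MMF_PK is 0.83 × 0.618 + 0.17 = 0.683. That is a spurious 13.5% advantage for MMF_PK, and 8.3% at f = 0.5. Tapering turns the bias round.

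**The case against.** The strongest reply is that truncation is not established. The Design section speaks about exactly these subjects and keeps them under observation to week 53, and the Discussion says much the same of those who leave for other therapy. The sentence in the Statistical analysis section may have been meant for full withdrawals only. On that reading both arms have 53 weeks and the figures above fall away. This stands as far as it goes, and it is why the point is conditional. But the sentence is unqualified, it is the stated reason for the weighting, and no passage says that steroid doses are part of the week-53 monitoring.

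A reader might infer that the MMF_BSA arm will look steroid-sparing. The document does not support that. It gives no doses, and the standardised regimen responds to the course of nephritis, so higher doses in non-responders are plausible. With a = 1.5 and f = 0.25 the truncated total is still lower in MMF_PK. Only the direction of the bias is settled.

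It can also be said that steroid use after failing the assigned strategy is a legitimate consequence of randomisation. That is so: a complete week-53 total is a valid comparison of policies. It does not isolate the two dosing methods.

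Finally, the window of an exploratory outcome is often left to the analysis plan. That lowers the severity. It does not remove a contradiction in the published text.

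**Conclusion.** The point holds in conditional form. The Design and Statistical analysis sections contradict each other on data after discontinuation. If the latter governs steroid data, mean accumulation is 40.9 weeks in MMF_BSA and 48.4 in MMF_PK at the planning rates. The unscaled total is then biased against the arm with more responders, by 18.5% at identical constant dosing and by 6.4% if the Part 2 dose is a quarter of the Part 1 dose. The proposed weighting cannot correct this. The direction of the bias assumes some steroid use by non-responders in Part 2, at similar levels in the two arms; the size rests on the planning rates and on assumed dose factors. If non-responders' doses are recorded to week 53, the truncation disappears and what remains is a mixture of strategies in Part 2. The outcome is exploratory, so severity is minor; the primary analysis is unaffected.

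**What to change.** 1. Reconcile the Design and Statistical analysis sections: state whether corticosteroid doses are recorded to week 53 for subjects discontinued at or before week 26.
2. Make the main between-arm steroid comparison the cumulative oral and intravenous dose from baseline to week 26. This window is common to all subjects and precedes both the switch and the week-26 discontinuations.
3. State how Part 1 dropouts enter that total, since the sample size allows for up to 14.3% attrition in Part 1.
4. Report a baseline-to-week-53 total as supportive only, and only if steroid data are collected to week 53 for all randomised subjects. Describe it as including the switch and treatment outside study management.
5. Do not use total dose divided by days observed where follow-up is unequal, and do not rely on inverse propensity weighting to restore week-26 non-responders.

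The cost is wording for one exploratory outcome. The standardised regimen already takes prior steroid dose as an input, so the week-26 total should need no new data. Only the supportive week-53 total could need extra collection, if monitoring of non-responders does not already cover steroid use.
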